### Harms

A few studies have reported that probiotics may cause infections and other adverse clinical events in critically ill patients [33, 34]. *Enterococcus faecalis*, which is used in the intervention, is a special probiotic that has also been reported as an opportunistic pathogen. However, the virulence factor detection of the *Enterococcus faecalis* species used in this study proved its safety with no virulence factor gene *IS16*, hyaluronidase gene, asa1, asa37 and hemolysin A. Our previous single-center study showed the safety of the probiotic capsule. If any adverse effects related to the intervention occur, they (as well as the solutions) will be recorded in detail in the CRF and EDC. If the intervention shows obvious harm to participants, the DMC has a full right to stop this study after informing all investigators.

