### Interventions, surgery and perioperative management

Patients in the probiotic group will receive three probiotic capsules (BIFICO, live combined *Bifidobacterium*, *Lactobacillus* and *Enterococcus* capsules, Shanghai Sine Pharmaceutical Co. Ltd., [name], Shanghai, China) containing *Bifidobacterium longum, Lactobacillus acidophilus,* and *Enterococcus faecalis* twice per day. Each capsule will contain > 1 * 10^7^ colony-forming units (CFUs) of live bacteria. Patients in the control group will be managed with a blank control. The intervention duration will begin from the end of the last cycle of NACT to postoperative day (POD) 7 or the discharge day. Adherence to the intervention protocols will be checked by telephone before admission to the surgical departments and making the rounds of the wards after admission. If any adverse event associated with the intervention occurs, the intervention will be stopped after evaluation by the investigators.

All enrolled patients will adhere to a perioperative enhanced recovery after surgery (ERAS) protocol [23]. The ERAS program involves preoperative prehabilitation [24] (including physical and respiratory training, nutritional support and psychosocial treatment), no preoperative mechanical bowel preparation, fasting 6 h before surgery and oral glucose solution ingestion allowed until 2 h before surgery, intraoperative target-oriented liquid management, local anesthesia in the deep incision, general anesthesia combined with epidural anesthesia, early removal of the urinary catheter and abdominal drainage tube, early bedside activity, multimodal postoperative analgesia, and postoperative early food ingestion under the guidance of surgeons (from liquid to semi-liquid then solid food according to the tolerance of patients).

Laparoscopic or DaVinci robotic radical gastrectomy will be performed by surgeons from the 22 hospitals whose capacity evaluation is described above. Surgical procedures will be guided by *Japanese Gastric Cancer Treatment Guidelines 2021 (6 th edition)* [2]. The type of digestive tract reconstruction will depend on the habits, intraoperative status and past experience of the surgeons, and the choice of laparoscopy- or DaVinci-assisted surgery will depend on the patients’ choice.

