### Outcomes

The primary outcome is the incidence of postoperative infectious complications, which are defined as bacterial infections occurring within 30 d after surgery. The definition of infectious complications is based on fever (≥ 38 °C), elevation of C-reactive protein (CRP), specific clinical symptoms of infection and positive bacterial culture. The diagnostic criteria for postoperative infections in this study are as follows. Pneumonia [25]: fever, cough, dyspnea, reduced arterial oxygen, typical pulmonary infiltrate on chest X-ray, positive culture from sputum or bronchoalveolar lavage. Urinary tract infection: obvious symptoms including frequent micturition, urgency to urinate, urodynia, leukocyturia, and a positive urine culture with > 10^5^ CFU/ml. Incision infection: redness or swelling of the incision, subcutaneous gas accumulation and purulent secretion and positive culture of incisional secretion [26]. Intraabdominal infection [27]: abdominal symptoms and positive signs such as abdominal pain, tenderness, rebound tenderness, radiographic evidence including intra-abdominal abscess, positive bacterial cultures from intra-abdominal smears or abdominal drainage fluid. Catheter-related blood stream infection: refer to the guidelines [28]. Systemic inflammatory response syndrome (SIRS): two or more of the following: a, temperature > 38 °C or < 36 °C; b, heart rate > 90/min; c, respiratory rate > 20/min or PaCO2 < 32 mm Hg (4.3 kPa); d, white blood cell count > 12 000/mm^3^ or < 4000/mm^3^ or > 10% immature bands [29]. The diagnosis of sepsis should follow the *Sepsis- 3 Consensus* [30].

Secondary outcomes for all participants include blood test results, such as the leukocyte count (WBC), percent of neutrophils (NEUT%), CRP and procalcitonin on PODs 1, 3, and 5; postoperative body temperature; length of postoperative hospital stay (LOS); total cost of hospitalization; 30-d readmission rate; 30-d mortality rate; duration of therapeutic antibiotic use; time to first flatus, first bowel movement and solid food tolerance; time to initiating adjuvant chemotherapy; EORTC QLQ-C30 score [31] on POD 30; PGSAS- 45 score [32] on PODs 3, 5 and 30; and visual analogue scale for pain evaluation on PODs 1, 3 and 5.

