## Monitoring

### Data monitoring and auditing

A data monitoring committee (DMC) consisting of surgeons, statisticians and ethics experts was established to improve the quality of this trial. The DMC remains independent of the research team of the project in order to objectively evaluate the effectiveness and safety. The interim analyses will be performed when half of the estimated participants (n = 159) are enrolled, and then important decisions will be made regarding whether to “continue the trial”, “continue the trial after adjusting the protocol” or “terminate the trial”. The results of the interim analysis will be released to all investigators. The auditing will be executed monthly by DMC based on CRFs and the EDC system.

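### Infection by the capsule's own organism is a named risk, but it is pooled into the primary endpoint and counted as a harm only if judged related, so an excess by arm could be masked

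*Protocol article*

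**What the plan says.** The intervention is a capsule "containing *Bifidobacterium longum, Lactobacillus acidophilus,* and *Enterococcus faecalis* twice per day" (Protocol article, Interventions, surgery and perioperative management). On risk, the Harms section says: "A few studies have reported that probiotics may cause infections and other adverse clinical events in critically ill patients". It adds that E. faecalis "is a special probiotic that has also been reported as an opportunistic pathogen", and answers this with negative virulence-gene tests and the earlier single-centre experience.

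On benefit, the Outcomes section says: "The primary outcome is the incidence of postoperative infectious complications", "which are defined as bacterial infections occurring within 30 d after surgery". Events are described by site or syndrome: pneumonia, urinary tract, incision, intra-abdominal, catheter-related bloodstream, SIRS and sepsis. Culture is part of several definitions; for intra-abdominal infection it is "positive bacterial cultures from intra-abdominal smears or abdominal drainage fluid". Neither the listed outcomes nor the listed subgroups include a count by organism.

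Three further provisions govern harm:
- Adverse effects are recorded in detail in the CRF and EDC if they are related to the intervention (Harms). The intervention is stopped for an associated adverse event after the investigators have evaluated it (Interventions). Nobody is blinded after assignment (Assignment of interventions).
- "The auditing will be executed monthly by DMC based on CRFs and the EDC system" (Data monitoring and auditing). The committee is independent and its remit covers safety as well as effectiveness.
- "If the intervention shows obvious harm to participants, the DMC has a full right to stop this study" (Harms).

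**The concern.** The harm that the article names is the same kind of event as the benefit it hopes to show. An infection with a capsule species in a probiotic patient is one more primary event. It becomes a recorded harm only through an individual attribution by someone who knows the arm. After gastrectomy, an abdominal infection yielding Enterococcus can easily be taken for an ordinary surgical complication, and the article gives no rule linking a cultured capsule species to the relatedness judgement.

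A modest excess of such infections is better seen by comparing arms than by judging cases one at a time, and the article describes no such comparison. If the product lowered other infections and caused a few of its own, the total would still look good. The specific safety question raised under Harms would then go unanswered.

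**Working it through.** **Inputs.** From Sample size: infection rates of 39.4% (control) and 15.2% (probiotic), one-sided alpha 0.025, power 80%, superiority threshold 10%, loss 10%, 159 per arm. The numbers of product-species infections below are assumptions; the article gives none.

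**The plan's own figure.** Two proportions with a non-zero null difference and unpooled variance:

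n = [0.394 × 0.606 + 0.152 × 0.848] × (1.960 + 0.842)² / (0.242 − 0.10)² = 143.1 per arm.

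143 / 0.9 = 158.9, so 159 per arm and 318 in total. The stated size reproduces, and nothing in this point changes it.

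**Expected totals.** 0.394 × 159 = 62.6, about 63 control events. 0.152 × 159 = 24.2, about 24 probiotic events. Fisher two-sided P for 24 v 63 of 159 is 1.3 × 10⁻⁶.

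**How many added infections can the total absorb?** Add k product-species infections to the 24 and recompute the difference with its unpooled 95% interval.

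| k | Probiotic v control (of 159) | Difference | Lower 95% limit | Chi-square P (uncorrected) |
|---|---|---|---|---|
| 0 | 24 v 63 | 0.245 | 0.151 | < 0.0001 |
| 7 | 31 v 63 | 0.201 | 0.103 | 0.0001 |
| 8 | 32 v 63 | 0.195 | 0.097 | 0.0001 |
| 22 | 46 v 63 | 0.107 | 0.003 | 0.045 |
| 23 | 47 v 63 | 0.101 | −0.003 | 0.059 |

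For k = 7: SE = √(0.396 × 0.604/159 + 0.195 × 0.805/159) = 0.0499, and 0.201 − 1.96 × 0.0499 = 0.103. The total still clears the 10% threshold with 7 added infections, and clears zero with 22.

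With 143 evaluable per arm (22 v 56) the room is smaller: the lower limit is 0.108 at k = 4 and 0.093 at k = 6.

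**What would a separate count show?** Fisher two-sided, 159 per arm:
- 5 v 0: P = 0.061
- 6 v 0: P = 0.030
- 7 v 0: P = 0.015
- 5 v 1: P = 0.21
- 7 v 1: P = 0.067

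**Plausible size.** If the true product-species infection rate were 1% to 5% (an assumed range), 159 × 0.01 = 1.6 to 159 × 0.05 = 8.0 cases would be expected in the probiotic arm. About 80 probiotic patients are expected at the interim analysis, which gives 0.8 to 4.0 cases.

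**The case against.** The strongest reply is that the article does give harm a route. The DMC audits case-level records every month, its power to stop for obvious harm is not tied to the infection total, and related effects are recorded in detail. A reader might infer that the harm stop cannot respond to these infections, or that the DMC sees only pooled totals. The text supports neither. A recognised E. faecalis bloodstream infection could reach the committee.

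Nor do investigators lack microbiological information. Culture is part of the endpoint definition, and therapeutic antibiotics are guided partly by bacteriologic evidence. What is absent is a stated link from a cultured species to the relatedness judgement.

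A reader might also infer that pooling biases the efficacy result. It does not. Each product-species infection counts against the probiotic arm, and all-cause infection is a legitimate net measure.

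Two further replies carry weight. The illustrative counts are assumed, and with even one background case in the control arm a small excess would often not reach significance (7 v 1: P = 0.067). The article also condenses a fuller protocol, and the CRF, SAP or committee charter may already hold an organism listing.

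These replies narrow the point but leave its core. The article itself places the named risk inside the efficacy endpoint and makes its recording as a harm depend on individual attribution without blinding.

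**Conclusion.** The point holds as a weakness in harm detection. As described, an excess of product-species infections in the probiotic arm could be masked by a favourable total. At the planning rates with 159 per arm, 7 added infections would leave the pooled result above the 10% threshold, while a separate count of 6 v 0 would give P = 0.03.

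This rests on the planning rates being roughly right and on assumed organism counts. The calculation shows only that masking is possible; it is no evidence that the product causes infections. It leaves the sample size and the validity of the primary comparison untouched. A favourable total alone, however, would not answer the safety question raised under Harms.

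**What to change.** Enter the species from every positive culture report, in both arms, in the EDC. Tabulate by arm the infections yielding Enterococcus, Lactobacillus or Bifidobacterium, with bloodstream infections shown separately and without regard to the relatedness judgement. Report this as a descriptive safety table in the final analysis, and give it to the DMC while the trial is running. Trial status says that recruitment is complete and that the trial ended during peer review, so the final table, compiled from existing culture reports, may be all that is still possible.

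The cost is one or two data fields and one table, with no extra patients and no change to the endpoint. The downside is that a species match does not prove the product strain and counts will be small. The table must be read against the control arm and does not by itself settle causation.

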### Assignment of interventions

A central dynamic, stratified strategy was adopted for the aim of randomization. The sequence of randomization was generated by a certain statistician who was independent of this trial using the method of Pocock-Simon minimization by SAS 9.3 (SAS Institute Inc., Cary, NC, USA) and stratified by age (< 65 years old or ≥ 65), tumor location (upper, middle or lower) and preoperative chemotherapy cycles (2 or ≥ 2 cycle). The stratification information provided by the investigators was submitted to the statistician who was responsible for executing randomization. Consequently, the allocation information will then be sent back to each participating site, and investigators will assign given interventions. The statistician is the only one who will know the allocation sequence to ensure that the sequence is concealed until the interventions are assigned.

Due to the open-label design of this study, no one will be blinded after assignment to interventions. After receiving the allocation information, investigators from every participating center will assign the given interventions to participants.

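### Adverse-event recording is stated only for effects judged related to the probiotic, so events outside the listed outcomes, including those before surgery, have no control-arm comparator

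*Protocol article*

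**What the plan says.** In the protocol article, Monitoring, Harms, the recording rule is: "If any adverse effects related to the intervention occur, they (as well as the solutions) will be recorded in detail". The section on interventions, surgery and perioperative management applies the same filter when it describes what follows an event: "If any adverse event associated with the intervention occurs, the intervention will be stopped after evaluation by the investigators". No other section shown gives a rule for recording adverse events, and the Outcomes section does not list them.

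The comparator is no treatment: "Patients in the control group will be managed with a blank control". Allocation is known to all: "Due to the open-label design of this study, no one will be blinded after assignment to interventions".

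The Harms section treats the risk as real. It notes that "A few studies have reported that probiotics may cause infections and other adverse clinical events in critically ill patients", and says of *Enterococcus faecalis*, one of the three species in the product, that it "is a special probiotic that has also been reported as an opportunistic pathogen". It then reports that testing of the strain used found none of the listed virulence genes. On monitoring it says: "If the intervention shows obvious harm to participants, the DMC has a full right to stop this study". Under Data monitoring and auditing, the DMC evaluates effectiveness and safety, and audits the case report forms (CRFs) and the electronic data capture (EDC) system monthly.

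**The concern.** A recording rule that depends on relatedness works differently in the two arms. A patient who takes no product cannot have an effect related to it, so the control count under this rule is zero by construction. The probiotic count depends on how readily unblinded staff attribute events to the product. The article's own limitations paragraph concedes that surgeons' subjectivity may affect results in an open-label trial.

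At stake is what can be said about safety outside the listed outcomes. Without a control background, a count of related effects cannot separate an excess from ordinary events after chemotherapy and around gastrectomy. It also cannot show that there was no excess. An analysis plan cannot repair this later, because events that were not captured cannot be recovered.

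**Working it through.** **Step 1: what is captured in both arms.** The Outcomes section applies to all participants. Set against the Harms section:

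| Type of event | Captured in both arms regardless of cause? | Source |
|---|---|---|
| Bacterial infection to 30 days after surgery, by site; SIRS and sepsis criteria | Yes | Primary outcome |
| Death and readmission to 30 days | Yes | Secondary outcomes |
| Therapeutic antibiotic duration, temperature, WBC, neutrophils, CRP, procalcitonin | Yes | Secondary outcomes |
| Pain, symptom and quality-of-life scores at set postoperative days | Yes | Secondary outcomes |
| Other non-infectious events after surgery | Not stated; only if judged related | Harms |
| Any adverse event between start of dosing and surgery | Not stated; only if judged related | Harms |

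The first four rows cover the main harm that the article names. The last two are the gap.

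**Step 2: how much exposure lies before surgery.** Dosing starts at the end of the last chemotherapy cycle and ends on postoperative day 7 or at discharge. Eligibility requires chemotherapy to have been completed 3 to 6 weeks before surgery. Preoperative exposure is therefore about 21 to 42 days, and postoperative exposure at most about 7 days. The preoperative share is about 21/(21 + 7) = 75% to 42/(42 + 7) = 86%. This assumes dosing from the end of chemotherapy; patients enrolled later have a shorter preoperative period. The clinical outcomes in the table start at surgery. The only preoperative contact that the article states is a telephone check of adherence.

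**Step 3: the denominator.** The planned 159 per arm reproduces from the Sample size section: [0.394 × 0.606 + 0.152 × 0.848] × (1.960 + 0.842)² / (0.242 − 0.10)² = 143.1, and 143.1/0.9 = 159.0. The point does not depend on this figure.

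**Step 4: what the rule records (illustration).** Let q be the true event rate in the probiotic arm and f the share of its events judged related. Expected recorded events are 159 × q × f in the probiotic arm and 0 in the control arm. Neither q nor f is in the documents; both are assumptions.

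| q | True events in probiotic arm | Recorded, f = 10% | f = 25% | f = 50% | Recorded in control |
|---|---|---|---|---|---|
| 5% | 8.0 | 0.8 | 2.0 | 4.0 | 0 |
| 10% | 15.9 | 1.6 | 4.0 | 8.0 | 0 |
| 20% | 31.8 | 3.2 | 8.0 | 15.9 | 0 |

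The control rate does not enter the formula. A recorded 8 against 0 arises from q = 10% with f = 50% and equally from q = 20% with f = 25%. In either case the true control rate could be lower, equal or higher. The recorded counts therefore carry no information about the difference between arms.

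**Step 5: what recording in both arms would give.** With 159 per arm and a two-sided 0.05 test, power is about 39% for 5% v 10%, 71% for 10% v 20% and 85% for 5% v 15%. The trial is large enough to detect a substantial excess if the events are captured in both arms, though not a small one.

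**The case against.** The strongest reply is that the trial already measures the harm that matters. Infection is the specific risk named in the Harms section. It is also the primary outcome, counted in both arms whatever its cause. Deaths, readmissions, antibiotic use and inflammatory markers are also two-armed, and the DMC sees the CRFs and the EDC data. This stands. A reader might infer that the control arm has no adverse-event data, or that harm cannot be compared or monitored at all. The Outcomes and Monitoring sections contradict both.

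Secondly, the article says that related effects will be recorded in detail; it does not say that other events will go unrecorded. The exclusivity is inferred. The schedule of assessments is in a figure that is not shown, and a fuller protocol or CRF may list adverse events for both arms. This stands as a caution and limits the point to what is stated. It does not remove the point, because the article states a criterion, and uses it twice, rather than merely leaving a detail out.

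Thirdly, no between-arm test of related effects is planned. A reader might infer that a spurious significant difference will be reported. The documents do not support that, so the illustration above gives counts and no P values.

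Finally, the article reports that recruitment is complete and that the trial ended during peer review, so a wider form may no longer be possible. That changes the remedy but not the gap.

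**Conclusion.** The point holds in a limited form. As stated, adverse-event recording depends on open-label attribution to a product that one arm never receives. Two classes of event therefore have no stated control-arm comparator for the analysis or the DMC: non-infectious events outside the listed outcomes, and all events during the roughly 3 to 6 weeks of preoperative exposure. By the planned schedule, that period is about three quarters or more of the time on product. The size of any resulting distortion is unknown, because the documents give neither background rates nor attribution shares.

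The primary analysis is unaffected, as is the comparison of postoperative infection, death and readmission. The conclusion rests on the article's wording and assumes that no unshown document provides for recording in both arms regardless of cause.

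**What to change.** If any collection remains open, record adverse events in both arms from randomisation to postoperative day 30, by the same procedure and at the same contacts, regardless of attribution. Keep relatedness as a separate field and tabulate by arm, for the DMC as well as the final analysis. If the full protocol or CRF already provides for this, the article should say so.

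If collection has closed:
- Do not present counts of related effects as a comparative safety analysis or as evidence of safety.
- Tabulate by arm the infections by type, readmissions and deaths already collected. Add culture isolates by species, flagging the three product species, where these were recorded; the article does not say that they were.
- State that preoperative events, and other events outside the outcomes, were captured only if judged related.

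The cost is a wider adverse-event form in the first case, and a few tables and a sentence of disclosure in the second. Neither changes the sample size or the primary analysis.
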